**Methods:**

A 2-arm randomized controlled trial with a parallel assignment of 1:1, with no blinding of study intervention, was performed. Eligible participants are consenting people living with HIV aged 18-29 years who receive HIV care at the study center and whose mobile phones support WhatsApp. Following informed consent and a baseline survey on clinical and personal preferences (eg, timing and frequency of messages), participants are randomized to the control group (messages designed by the research team) or to the experimental group (messages designed by participants), stratified by sex, educational level, current ART intake, and history of ART abandonment. Participants in both groups receive up to 3 WhatsApp messages per week for 16 weeks. ART adherence, the primary outcome, is measured using the Simplified Medication Adherence Questionnaire (SMAQ) at 4, 8, 12, and 16 weeks. Monthly feedback questionnaires on user experience are also administered. The WhatsApp chat format allows two-way communication between participants and the research team throughout the study. We will compare ART adherence between 2 groups at 16 weeks under the intention-to-treat principle, with no interim analysis planned. Based on an estimated 10% difference in adherence, 78.9% power, and a 2-sided α of .05, the target sample size was set at 120, later increased to 131 to include a 2-week pilot phase.

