### Study Design

A randomized controlled trial with 2 arms and a 1:1 assignment ratio will be conducted.

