### Sample Size Determination

The sample size calculus considered a 95% CI and the assumption of a 10% difference in optimal ART adherence between study groups (90% in the self-designed group versus 80% in the standardized group by the end of the study). Accounting for a power level of 78.9%, the obtained result was 120 (EPIDAT 4.0). To account for a 2-week pilot phase, we increased the sample size to 131 participants.

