### Data Collection

For this study, data collection and management use REDCap electronic data capture tools hosted at Universidad Peruana Cayetano Heredia [24]. The enrollment form collects participants’ baseline sociodemographic data, history of ART, strategies for taking ART, assessment of their adherence with the SMAQ, depression screening, stigma, an evaluation of their satisfaction with the health services provided at the study center, and a measurement of their knowledge about ART and adherence. For participants allocated to the self-designed messages arm, we also register their created messages in REDCap. In total, 4 members of the research team are involved in data collection. The PI trained them with mock interviews and a web-based course on using REDCap.

We used an intermediate Excel file hosted in a secured drive to schedule messaging and questionnaire delivery per participant through the web-based study platform. This file contains the identification codes, a list of messages, and the date and time of sending.

The web-based study platform collects CSV file data on every message and questionnaire scheduled, sent, received, read, and answered per participant and chat sessions with providers. The records include anonymous hour-dated logs of all conversation contents with participants, including reasons for adding, modifying, or eliminating messages in the self-designed group and responses to study questionnaires.

To obtain the total number of eligible patients who meet eligibility criteria, independent of whether they are invited to participate, we collect routine data from the study center regarding the number of outpatient consults and patients in the age group of interest who pick up ART during the study period.

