### Data Analysis Plan

The primary outcome variable is ART adherence, primarily measured as a binary variable defined by the SMAQ results at 4, 8, 12, and 16 weeks of intervention. For the analysis of the primary outcome, and with an intention-to-treat approach, we will compare between both study groups the proportion of participants adherent to ART at 16 weeks of intervention with bivariate (chi-square) and multivariate (logistic regression) analyses. We will build the multivariate logistic regression model with a stepwise approach (forward selection and backward deletion), adding 1 explanatory variable at a time and starting with the explanatory variables with the highest theoretical value and strength of association with the primary outcome in bivariate analyses. At each step of model building, we will check variations in the reported odds ratios and standard errors to define the retention or removal of explanatory variables. Irrespective of bivariate association, the study group variable and potential confounders, notably history of ART abandonment, ART pick-up visits during the study period, and time of permanence in the study, will be entered into the model. We will test the final model fit with Hosmer and Lemeshow goodness-of-fit test and report results with adjusted odds ratios and 95% CIs. Preliminary outcome analyses will not be performed since they require multiple measurements, and the intervention is relatively short. We will not perform multiplicity adjustments.

With mixed models for repeated measures, we will explore the changes in ART adherence, as determined by SMAQ, from baseline to 4, 8, 12, and 16 weeks on the intention-to-treat population, with no imputation of missing data. In this model, the change from baseline value will be the dependent variable, with participant random effect and baseline ART adherence, intervention group, and measurement time as the primary fixed factors. We will check linearity assumptions for time and use participants’ unstructured covariance structure. Two-sided 95% CIs for the mean change within each study group will be calculated.

To compare the time of study permanence in both study groups, we will perform survival analysis and compare hazard ratios for study loss to follow-up between study groups, according to the study definitions. This definition lets us know how many participants are active each week of intervention.

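### With only about 18-20 non-adherent participants expected, the adjusted week-16 odds ratio would be better estimated by a Firth-penalised fit, and a passed Hosmer-Lemeshow test should not count as evidence of fit

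*Protocol article*

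**What the plan says.** The Data Analysis Plan compares week-16 adherence between arms with a chi-square test and a logistic regression. The regression is built stepwise. Study group is always kept, as are at least three named covariates: previous abandonment of treatment, medication pick-ups while on study, and length of stay in the study. The plan then states: "We will test the final model fit with Hosmer and Lemeshow goodness-of-fit test and report results with adjusted odds ratios and 95% CIs". It names no estimator, no number of candidate covariates and no acceptance rule for the fit test.

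Sample Size Determination gives the assumed adherence as "90% in the self-designed group versus 80% in the standardized group by the end of the study", with 120 participants, and adds: "To account for a 2-week pilot phase, we increased the sample size to 131 participants". Study Design sets 1:1 allocation. Among the items that Data Collection lists on the enrollment form are "depression screening, stigma, an evaluation of their satisfaction with the health services provided at the study center". The limitations paragraph of the Discussion concedes that the sample size assumes everyone answers the final questionnaire, which may not happen.

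**The concern.** The information in a binary model is governed by the smaller outcome class, here the non-adherent. With few of them and several coefficients, maximum-likelihood logistic regression moves a non-null log odds ratio away from zero and has more variance than a penalised fit. The adjusted odds ratio is the only between-group effect for which the article promises a confidence interval; the other intervals it mentions are for change within each arm. If the message types truly differ, the headline figure will on average be somewhat too large. A fit test with little power may then seem to endorse it.

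**Working it through.** **Inputs.** Adherence 90% and 80%; N = 120, then 131; 1:1 allocation (Sample Size Determination, Study Design). Two-sided alpha 0.05 and 78.9% power (Abstract, Methods). At least four model terms (Data Analysis Plan).

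**The plan's own figure.** The article gives no event count, so its sample size is checked first. Power = Φ{(|d|√n − 1.96√(2p̄q̄)) / √(p₁q₁ + p₂q₂)}, with n per arm.

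- 90% v 80%, n = 60: (0.7746 − 1.96 × 0.5050) / 0.5 = −0.430, so power is 33.3%, not 78.9%.
- 90% v 70%, n = 60: (1.5492 − 1.96 × 0.5657) / 0.5477 = 0.804, so power is 78.9%.

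That mismatch is a separate matter. It matters here because the event count depends on the rates, so both sets are carried forward.

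**Expected non-adherent participants.**

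- 90/80: 60 × 0.10 + 60 × 0.20 = 18; for 131, 131 × 0.15 = 19.65.
- 90/80 with 80-90% response: 14.4-16.2 of 120; 15.7-17.7 of 131.
- 90/70: 60 × 0.10 + 60 × 0.30 = 24; for 131, 131 × 0.20 = 26.2.

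Per forced term at 90/80: 18/4 = 4.5 and 19.65/4 = 4.9. At 90/70: 24/4 = 6 and 26.2/4 = 6.6.

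**Bias of the adjusted log odds ratio.** True odds ratio (0.9/0.1)/(0.8/0.2) = 2.25, log 0.811. Simulation with 12,000 trials per setting and 15% non-adherent overall. Assumed independent covariates: one binary (30%, log odds ratio 0.7), two continuous (0.5 per SD), the rest null. No stepwise search was simulated.

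| N | Covariates besides arm | Mean ML log OR (as OR) | Bias | Firth, as OR |
|---|---|---|---|---|
| 120 | 0 | 0.864 (2.37) | +6.6% | 2.26 |
| 120 | 3 | 0.883 (2.42) | +8.9% | 2.24 |
| 120 | 6 | 0.936 (2.55) | +15.4% | 2.26 |
| 131 | 0 | 0.865 (2.37) | +6.6% | 2.27 |
| 131 | 3 | 0.886 (2.42) | +9.2% | 2.25 |
| 131 | 6 | 0.924 (2.52) | +13.9% | 2.26 |

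Other assumed covariate mixes at N = 131 gave about +7% to +10% with three covariates and +13% to +14% with six.

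- *Size beside imprecision.* Three covariates, N = 131: (0.886 − 0.811)/0.61 = 0.12 standard errors. Six covariates, N = 120: (0.936 − 0.811)/0.70 = 0.18. The unadjusted 95% interval at the design values uses SE = √(1/6 + 1/54 + 1/12 + 1/48) = 0.538, giving 0.78 to 6.46.
- *Null and coverage.* At a true odds ratio of 1, the mean ML estimate is 0.99. Coverage of the ML 95% interval is 94.8-96.2%, and null rejection of the Wald test is 5-6%.
- *Noise.* At N = 131 the Firth fit lowers the root mean squared error of the log odds ratio by about 11-15%. In one mix with six covariates it falls from 0.68 to 0.57, which is 0.11/0.68 = 16%.

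**Hosmer-Lemeshow.** Expected non-adherent per decile is 18/10 = 1.8, or 19.65/10 = 2.0. With an omitted quadratic or interaction term the test rejects in 9-14% of trials, and in 15.4% under another covariate mix. With a correct model it rejects in 4-6%. At N = 1200 the same kind of misspecification (quadratic) is detected in 71%.

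**The case against.** The best reply is that the article never says ordinary or unpenalised. The estimator is a detail that an unseen statistical analysis plan could fix, and if it already names a penalised fit, the estimation point falls away. What stands is that unqualified logistic regression is normally read as maximum likelihood, and nothing in the article signals otherwise.

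Second, the bias is small: 0.1-0.2 of a standard error. Study group alone already gives about +7%, so the three forced covariates add only about 2 percentage points. The chi-square comparison is untouched. All of this is correct, and it limits the weight of the point.

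A reader might infer more than the documents support:

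- *That the estimate is always pushed away from 1, or the inference is invalid.* There is no shift at an odds ratio of 1, and size and coverage hold.
- *That the overstatement reaches about 20% or more, with frequent separation.* Such figures need eight or more covariates, or substantial non-response with a larger model. The enrollment-form items are data collected and not a stated list of candidates. Separation in 5-10% of trials was seen for some coefficient of a seven-term model, not for the treatment effect, and the plan's stepwise check on odds ratios and standard errors would tend to expose it.
- *That Hosmer-Lemeshow is worthless, or a gate the model must pass.* It has very little power, not none, and no acceptance rule is stated. Deleting it would change no estimate.

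**Conclusion.** The point holds as a cheap improvement of minor to moderate weight. At 90% versus 80%, about 18-20 non-adherent participants support at least four forced terms (24-26 at 90% versus 70%, fewer with non-response). Under maximum likelihood a real log odds ratio is overstated by about 7-10% with the forced terms and about 13-15% with six covariates. A Firth fit removes nearly all of this and reduces the noise. A non-significant Hosmer-Lemeshow result is almost no reassurance.

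This rests on the design rates, on reading logistic regression as maximum likelihood, and on assumed covariate effects. Because the planned stepwise search was not simulated, the figures describe fixed models and not the exact final model. The sample-size mismatch and the adjustment for post-randomisation variables are separate and weigh more, but curing them would not remove this bias.

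**What to change.** State that the adjusted week-16 odds ratio will be estimated by Firth-penalised logistic regression with penalised profile-likelihood 95% confidence intervals, on a prespecified set of baseline covariates. If predicted or standardised risks are also reported, use the intercept-corrected Firth fit. Add that a non-significant Hosmer-Lemeshow result will not be taken as evidence of adequate fit; the test may stay as a description.

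The cost is one or two sentences, and the method is available in standard software. The downside is a slightly less favourable reported odds ratio. The article reports data curation as of February 2025, so the change should be dated and made before outcomes are compared by arm, if that is still possible.

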### Study Procedures—Preimplementation Phase

First, during the study's design, we consulted with health staff to better respond to the study’s population needs without disrupting routine HIV program operations. Once the study design was completed, the coordination was intended to communicate study standard procedures and facilitate the study's implementation. Our institutional review board (IRB) approved the full study protocol in July 2023. Then, we designed the web-based study platform with Infobox Latinoamérica, a Peruvian IT company. The web-based study platform is integrated with WhatsApp business and supports the delivery of personalized and standardized messages, a Chatbot for mass-sending questionnaires and continuous chat with participants. The Infobox provides technical support during the study as required.

The principal investigator (PI) completed the web-based training on BCT-Taxonomy to design the standardized messages. He created 44 standardized messages, each corresponding to one of 14 selected BCT categories, though the final format considered elements of other behavior change theories (health belief model, social support theory, and social cognitive theory). The number of standardized messages minimized the chance of participants receiving repeated messages during the study period. Table S1 in Multimedia Appendix 1 lists all standardized messages with their corresponding BCTs in the order those messages are sent to participants.

We created the randomization sequence using the REDCap (Research Electronic Data Capture) randomization module (REDCap Consortium); sex assigned at birth, educational level, current ART intake, and previous ART abandonment were the criteria for stratified randomization.

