### Study Procedures—Implementation Phase

To preserve confidentiality, nurses from the HIV Program are informed about the study’s eligibility criteria and collaborate to identify potential participants. While they wait for infectious diseases outpatient consults or ART pick-ups, the nurses inform them about the study. For those interested, we reassess eligibility, explain the study in detail, and obtain informed consent privately (a model of our consent form is shown in Multimedia Appendix 2). Then, we fill out a REDCap baseline questionnaire, collect data to send messages through the study web-based platform, and, when applicable, explain and support the process of self-designing the messages. Figure 1 presents participant identification, recruitment, and allocation. After completing the baseline questionnaire, which provides information for stratification (sex assigned at birth, educational level, current ART intake, and previous ART abandonment), participants are randomized to one of 2 study arms allocated with a 1:1 proportion. Then, the research staff informs participants of their assigned group and provides details accordingly. Given the characteristics of the intervention, neither the researchers nor the participants are blinded.

Participants allocated to the self-designed messages group draft 10-15 messages that would help them take their ART; this number assures similitude in the number of messages received per participant in both study arms. Message creation is done during enrollment. Participants determine the final content of their messages. However, during their creation, the research staff ensures that the content excludes potentially harmful or offensive topics. If there are any doubts during the process, the staff provides support by offering examples based on characteristics identified during the baseline questionnaires and general conversation with participants (such as family, personal hobbies, goals, and other general topics). After the messages are created, the data manager reviews them and may slightly modify them to ensure clarity while keeping the original content. Once the messages are ready, the data manager enters them into the study messaging platform.

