**Figure 1 figure1:**
[figure not shown]
Participant identification, recruitment, and allocation. ART: antiretroviral therapy; REDCap: Research Electronic Data Capture; SMAQ: Simplified Medication Adherence Questionnaire.

During 16 weeks from the date of enrollment, participants receive up to 3 intervention messages per week; they are requested to reply briefly once they read those messages. Weekly, the data manager schedules the delivery of messages according to participants’ preferences, as recorded on REDCap, and monthly questionnaires. During the study, participants can chat with 2 medical doctors on the web-based study platform to ask about health issues, navigate the health system, and schedule infectious disease outpatient consultations (the standard of care requires in-person scheduling). If a participant requests modifications or additions to self-designed messages during the chat, the physician responsible for monitoring the chat will review the new messages initially. The PI will be notified if any content is deemed harmful or inappropriate. He will then contact the participant to explain the reasons for rejecting the message and will request an alternative message. This review process will continue with oversight from the data manager until the accepted messages are included in the platform’s system. Additionally, if physicians responsible for monitoring the platform identify inappropriate content during chat conversations, they will address this with all parties involved non-punitively and constructively. They will explain why the content is inappropriate and direct the conversation to ensure it remains safe and respectful.

As a follow-up, participants receive WhatsApp questionnaires every 4 weeks after enrollment and 2 days apart to assess (1) adherence to ART and (2) user experience with the intervention delivery. After 16 weeks of intervention, participants receive a final message acknowledging their participation and reminding them that the messages will stop.

Participants may withdraw from the intervention at any time by sending a message through the chat platform, responding to messages sent as part of the intervention, or contacting research team members during a medication pick-up visit. The participant will be told that withdrawing from the study does not affect their usual care at the study center. The data manager will register that patient as “withdrawn” in REDCap, and no more messages will be sent.

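### Within-arm change from baseline in SMAQ adherence is mixed with a switch from a staff-completed baseline questionnaire to WhatsApp questionnaires at follow-up

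*Protocol article*

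**What the plan says.** **Baseline.** The Implementation Phase section describes recruitment at the hospital: "While they wait for infectious diseases outpatient consults or ART pick-ups, the nurses inform them about the study". After private consent, "Then, we fill out a REDCap baseline questionnaire, collect data to send messages through the study web-based platform". Randomization follows once that questionnaire is complete. The Data Collection section lists the SMAQ among the contents of the enrollment form ("assessment of their adherence with the SMAQ, depression screening, stigma") and says of the data collectors: "The PI trained them with mock interviews and a web-based course on using REDCap".

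**Follow-up.** The Implementation Phase section, in the text after Figure 1, says that "participants receive WhatsApp questionnaires every 4 weeks after enrollment and 2 days apart to assess (1) adherence to ART". The Preimplementation Phase section describes the delivery tool as including "a Chatbot for mass-sending questionnaires and continuous chat with participants". Under Data Collection, the responses are held in the platform's own logs.

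**Analysis.** For the exploratory repeated-measures model, the Data Analysis Plan says that "we will explore the changes in ART adherence, as determined by SMAQ, from baseline to 4, 8, 12, and 16 weeks", and then: "In this model, the change from baseline value will be the dependent variable". Baseline adherence, arm and time are fixed factors, and a two-sided 95% CI is planned for the mean change in each arm.

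Nowhere does the article describe a WhatsApp SMAQ at baseline, a staff-completed SMAQ at follow-up, or a check of agreement between the two. The limitations in the Discussion mention self-report but not the change of mode.

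**The concern.** A person may answer questions about missed doses differently to a member of staff at the clinic than in a WhatsApp questionnaire. If so, subtracting one kind of answer from the other gives a difference that contains the reporting shift as well as any change in behavior. Randomization does not remove this from a within-arm quantity, because the shift sits inside every change score in both arms.

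The within-arm change is likely to be read as evidence. The Discussion sets out two aims: whether WhatsApp messaging improves adherence, and whether the two message types differ. Both arms receive messages, so readers looking for an answer to the first aim will turn to the change from baseline in each arm. That quantity already lacks a control. The mode switch is a separate defect, because the two measurements are not made in the same way.

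**Working it through.** The plan gives no figure for a mode effect, so there is nothing to reproduce. The check has three parts: the logic, an illustration of size, and the effect of the fix on the planned model.

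**1. What the shift touches.** Let p(t) be the proportion that would be adherent at week t under the baseline mode, and m the shift in the reported proportion from moving to WhatsApp.

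- Expected report at baseline: p(0). At weeks 4, 8, 12 and 16: p(t) + m.
- Within-arm change from baseline: p(t) − p(0) + m. The shift stays in.
- Between-arm contrast in change, arms S (self-designed) and C (standardized): [pS(t) − pS(0) + m] − [pC(t) − pC(0) + m]. The shift cancels if m is the same in both arms.
- Week-16 primary contrast: [pS(16) + m] − [pC(16) + m]. Both sides use one mode.
- Course from week 4 to week 16 within an arm: [p(16) + m] − [p(4) + m]. The shift cancels if m is stable over follow-up.

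An indicator for mode is 0 at baseline and 1 at every later week, for every participant. It is the same variable as baseline versus follow-up, so no covariate, random effect or covariance structure can estimate m.

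**2. Size, for illustration only.** The documents give arm sizes of 60 (120/2) and about 65 (131/2). The other inputs are assumptions: yes/no SMAQ status, 80% adherent at baseline, within-person correlation 0.3 or 0.5, no true change, complete data, and a common shift of −10 to +10 points. There were 20,000 simulated trials per setting.

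| Shift m (points) | Mean within-arm change (points) | Within-arm 95% CI excludes 0 |
|---|---|---|
| −10 | −10 | 33.4% to 47.0% |
| −5 | −5 | 12.6% to 16.1% |
| 0 | 0 | 4.5% to 5.5% |
| +5 | +5 | 14.3% to 17.0% |
| +10 | +10 | 44.5% to 61.2% |

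Across all settings the between-arm difference in change averaged about 0 and was rejected in 5.0% to 5.7% of trials.

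Two cells can be confirmed by hand:

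- m = −10, n = 60, correlation 0.3. Covariance = 0.3 × √(0.16 × 0.21) = 0.055. Adherent both times = 0.8 × 0.7 + 0.055 = 0.615. Discordant = (0.8 − 0.615) + (0.7 − 0.615) = 0.270. SE = √[(0.270 − 0.10²)/60] = 0.0658. Then 0.10/0.0658 = 1.52, and Φ(1.52 − 1.96) ≈ 0.33.
- m = +10, n = 65, correlation 0.5. Covariance = 0.5 × √(0.16 × 0.09) = 0.06. Adherent both times = 0.8 × 0.9 + 0.06 = 0.78. Discordant = 0.02 + 0.12 = 0.14. SE = √[(0.14 − 0.10²)/65] = 0.0447. Then 0.10/0.0447 = 2.24, and Φ(2.24 − 1.96) ≈ 0.61.

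**3. What changes if baseline is only a covariate.** The planned linear model is Y(t) − Y(0) = a + b·Y(0) + arm and time terms. Moving Y(0) across gives Y(t) = a + (b + 1)·Y(0) + the same arm and time terms. The arm and time coefficients are unchanged; only the coefficient on baseline differs. What drops out is the reported within-arm change.

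**The case against.** The strongest case against is that this touches nothing confirmatory. Change from baseline is not in the Outcomes section, and the Data Analysis Plan presents it as exploratory. The primary outcome and the adherence percentages at weeks 4, 8 and 12 are all collected by WhatsApp. Baseline adherence is already a fixed factor, so the arm contrasts barely depend on the choice of dependent variable. Within-arm change could not be credited to messaging in any case, since both arms receive messages. Week 4 is a post-randomization anchor with its own nonresponse, so keeping change from baseline with a caveat is defensible. All of this stands and limits the point to one descriptive quantity. It does not remove the point, because the plan commits to that quantity with an interval and the article carries no caveat.

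A reader might infer more than the documents support:

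- **That follow-up questionnaires are answered alone and away from any visit, so setting and timing are confounded too.** The article says neither. The Setting section says ART is usually dispensed monthly, so a questionnaire every 4 weeks could fall near a pick-up. That the baseline items were asked aloud is itself a reasonable inference from staff completion and mock-interview training, not a stated fact.
- **That both arms will seem to worsen, or to improve, by a known amount.** The documents give neither sign nor size. The shifts above are assumptions.
- **That the shift should be judged against the 10-point design difference.** That is a between-arm difference, which a common shift does not alter.

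**Conclusion.** The point holds in a limited form. The exploratory within-arm mean changes from baseline, and their 95% CIs, combine any change in adherence with a change in mode of administration, and the planned data cannot separate the two. The bias equals the mode shift, point for point, but the documents give no value for that shift. The simulated rates show only that a moderate shift could produce an apparently clear change where none occurred.

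Protection of the between-arm contrast in change rests on an equal shift in the two arms. The arms are unblinded, so this is plausible but not guaranteed. Baseline precedes randomization, so an unequal shift would mean that the arms answer the WhatsApp questionnaire differently at the same true adherence. That would be differential self-report, a separate matter from the change of mode.

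**What to change.** In the Data Analysis Plan, make SMAQ status at weeks 4, 8, 12 and 16 the dependent variable, with baseline SMAQ as a covariate only. Base inference on between-arm contrasts, and describe the time course within arms from week 4 to week 16, where the mode is constant. If within-arm change from baseline is still shown, label it as confounded with mode of administration and do not interpret it as a change in adherence. Name the change of mode in the limitations paragraph of the Discussion.

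The cost is analysis wording and one sentence of limitation; no new data are needed. The article reports enrollment complete and data curation under way, so the baseline mode can no longer be changed. The real loss is that the within-arm description no longer covers the first 4 weeks. The equality of arm and time terms shown above is for a linear model. If the binary status is modeled on the logit scale, the contrasts become odds ratios and will not match number for number.
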